## Abstract

**Introduction:**

Recanalisation of intracranial aneurysms following endovascular treatment is a major issue. Many factors, including aneurysm morphology, the method of treatment, and haemodynamics, are considered to be associated with recanalisation. However, the underlying haemodynamic mechanisms are not completely understood.

**Methods and analysis:**

This is a prospective, observational, registry study for patients with intracranial aneurysms who are treated endovascularly. It will enrol 200 eligible patients. Data on morphological, haemodynamic, and treatment factors will be collected prospectively. The advanced virtual stenting technique and porous media method will be used in haemodynamic simulations. The clinical and angiographic outcomes at 6 months will be measured and analysed. This observational study will determine the haemodynamic factors that affect the recanalisation of aneurysms.

**Ethics and dissemination:**

Both the study protocol and written informed consent were reviewed and approved by the Institutional Review Board of Beijing Tiantan Hospital (KY2016-023-01). The results of study will be disseminated in professional printed media.

**Trial registration number:**

NCT02812108; Pre-results.

Strengths and limitations of this studyThis is the first prospective registry study of aneurysm recanalisation mainly focusing on the haemodynamic effect after coil embolisation or stent-assisted coiling (or flow diverter).The advanced virtual stenting technique and porous media method will be used in haemodynamic simulations.The details of aneurysm wall thickness are unavailable in the endovascular procedure, and thus such information will be not used in the simulations.The assumption of rigid wall in the parent vessel and aneurysm will be used in the simulations and the aneurysm model will not change over the cardiac cycle. Additionally, laminar flow and Newtonian blood assumptions will be used in our computational fluid dynamics simulations. These assumptions may introduce bias in our simulation results.The simulations with three cardiac cycles may have a limited capacity to identify the features that are responsible for recanalisation occurring over the follow-up.Computational capacity limits the improvement of those assumptions and the haemodynamics may not fully explain the mechanism of recanalisation.

## Introduction

Due to its rapid development, endovascular treatment has become the first-line therapy for intracranial aneurysms (IAs).^1–3^ Endovascular treatment is associated with less invasiveness and lower morbidity compared with microsurgical clipping.^4^ However, recanalisation of aneurysms is a disadvantage of such a modality.^5–9^ Many factors, including complete initial embolisation, stent-assisted coiling, dense packing, and flow diverters, can reduce the recanalisation rate.^10–13^ The large size of aneurysm, wide neck, rupture status, and intraluminal thrombosis are risk factors of recanalisation of aneurysms.^6^
^9^ However, the haemodynamic mechanism has not been well studied and only a few studies have reviewed the relationship between haemodynamics and recanalisation of aneurysms. More importantly, no prospective cohort has analysed the haemodynamic risk factors affecting recanalisation of aneurysms and no high-level evidence has been obtained.

Haemodynamics play an important role in the initiation, growth and rupture of aneurysms.^7^
^8^
^14–16^ Previous studies have shown that haemodynamics are associated with outcomes of aneurysms after endovascular treatment. Studies have also shown that high wall shear stress and flow velocity are risk factors of recanalisation of aneurysms.^7^
^8^
^14^ However, these reports were retrospective studies with a small sample size, and no stent or flow diverter cases were involved. Outcomes of aneurysms after stent or flow diverter treatment via a haemodynamic method need to be prospectively analysed. As a future tool, simulations before the procedure may provide an optimal endovascular strategy to reduce the recanalisation rate at follow-up. Therefore, examining the haemodynamic predictors of recanalisation of aneurysms would of great value for clinical practice. In this observational study, we hypothesise that the haemodynamic mechanism plays an important role in the recanalisation of aneurysms after endovascular treatment. Additionally, the identified adverse haemodynamic factors could indicate a negative outcome of recanalisation.

## Methods and analysis

### Study design

Haemodynamic analysis for intracranial aneurysm recanalisation after endovascular treatment (HARET) is a prospective observational registry for patients with IAs who were treated endovascularly in our centre, and is sponsored by the National Nature Science Foundation of China. HARET was designed to examine the risk factors of recanalisation of aneurysms, based on evidence observed through the registry and measured by haemodynamic simulations and clinical practice. The goal of HARET is to reduce the recanalisation rate of IAs under endovascular treatment. This study was designed to investigate patients with endovascular treatment, including both conventional coil embolisation and flow diversion. After inclusion of data, in addition to the overall analysis of collected data, the subgroups of conventional coil embolisation and flow diversion will be created, analysed and compared. This is a single-centre study and the protocol will be performed at Beijing Tiantan Hospital, which is the largest neurointerventional centre in China. Patients with aneurysms who were treated endovascularly in our centre will be recruited. Institutional Review Board approval was obtained at Beijing Tiantan Hospital (KY2016-023-01). Patients or their relatives will be informed of the study and the anonymous collection of their data. These patients can withdraw from the study at any time. The study has been registered at http://www.trials.gov (NCT02812108). A diagram of the study protocol is shown in figure 1.

**Figure 1 BMJOPEN2016014261F1:**
[figure not shown]
Diagram of the protocol. IAs, intracranial aneurysms; CFD, computational fluid dynamics; M, months.

### Data collection and analysis

Data on patients, aneurysms, and treatment characteristics will be collected and recorded. The patient characteristics that will be recorded are age, sex, history of cigarette smoking and alcohol drinking, cholesterol/triglyceride values, any history of diabetes mellitus, hypertension, and coronary artery disease, and familial history of aneurysms. Characteristics of aneurysms that will be recorded are size, neck size, dome-to-neck ratio, dome-to-artery ratio, shape, location, clinical presentation, whether the aneurysm is ruptured or unruptured, and the number of aneurysms. Treatment-related factors will include treatment techniques, including coiling alone, balloon assistance, stent placement, or flow diverter treatment, the number of devices, packing density, and angiographic results.

Perioperative complications will be recorded and analysed. Immediate postoperative angiographic results and 6-month postoperative angiographic results will be collected. An independent angiographic committee will evaluate postoperative and 6-month occlusion of aneurysms, as well as the progress of occlusion of aneurysms. Occlusion of aneurysms will be evaluated using classification as complete occlusion, residual neck and residual aneurysm.^17^
^18^ Complete occlusion is defined as cases without any contrast media filling into the neck or sac of the aneurysm. The residual neck is defined as the existence of contrast media filling into the neck of the aneurysm on any single view projection, but without filling into the aneurysm sac. Any filling of the sac is classified as a residual aneurysm. Complete occlusion and a residual neck will be considered a satisfactory result, whereas a residual sac will be considered unsatisfactory. Progress of occlusion will be evaluated by direct comparison immediately after the operation with occlusion at 6 months, and described as one of three classes: improved, stable, or worse. Recurrence of aneurysms will be defined as any increase in contrast filling of aneurysms during follow-up.^18^ Angiographic follow-up will be routinely performed at 6 months after treatment. Clinical follow-up results will be analysed and recorded during hospitalisation for angiographic follow-up or by telephone interview using the modified Rankin scale score at 6 months. A modified Rankin scale score of 0–2 is a favourable outcome, and a score of 3–6 is an unfavourable outcome.

### Criteria

Inclusion criteria are: patients who are treated by the endovascular approach for intracranial aneurysm(s); patients older than 18 years; and patients who agree to participate in the study.

Exclusion criteria are: patients who have already been treated by the endovascular approach for an intracranial aneurysm; patients who have a brain arteriovenous malformation; patients who have a fusiform aneurysm; patients who have a dissecting aneurysm; patients who are being treated by parent vessel occlusion; patients who are being treated by a covered stent; and patients lacking three-dimensional (3D) aneurysm images or the images are not satisfactory for the simulation.

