We will then post-process and visualise the results of these simulations with the ANSYS CFD-Post. Haemodynamic parameters will be carefully examined at two regions: the aneurysm neck plane and the aneurysm dome. These parameters are wall shear stress, velocity, and pressure. The averaged and maximum values will be recorded. In addition to quantitative parameters, the qualitative parameter as inflow concentration will also be recorded. As described by Dhar *et al*,^24^ with estimation using multiple views of aneurysm geometries, the IA neck plane will be defined and created as the location from where the aneurysm sac pouches outward from the parent artery. Because flow in aneurysms before and after embolisation is different in each case, we will use the reduction ratio, which is calculated as: (parameter_pre_−parameter_post_)/parameter_pre_. This is a normalised parameter to allow comparison among different patients.^14^

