### Sample size and data analysis

No prospective data are available regarding haemodynamic predictors of aneurysm recurrence after endovascular treatment. According to our previous retrospective study,^14^
^25^ the recurrence rate of aneurysms was approximately 10%. A mean reduction in flow velocity of 20%±10% was associated with recurrence, and a reduction of 30%±15% was associated with stability. A sample size of 150 patients will be included with a two-sided significance level of 5% and a power of 80%. The rate of included patients that will be lost to follow-up is assumed to be 10%, and a sample size of 167 patients will be needed. Finally, a total of 200 patients will be enrolled.

Data will be presented as mean and SD for quantitative variables or frequency for qualitative variables. Analysis of factors affecting angiographic and clinical outcomes will be performed. Potential associations between patients, aneurysms, procedural characteristics, or haemodynamic parameters and outcomes will be assessed by univariate analysis using the Student's *t*-test, the Wilcoxon test, the χ^2^ test, or Fisher's exact test, as appropriate, and by multivariate analysis. Logistic regression will include all variables with p<0.20 by univariate analysis. Statistical significance will be recognised when p<0.05. Statistical analysis will be performed using IBM SPSS Statistics for Windows, V.21.0 (IBM Corp, Armonk, New York, USA).

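### The unit of analysis is not fixed: patients are counted, angiographic recurrence and haemodynamics belong to aneurysms, and the named tests are valid only with one record per patient

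*Protocol article*

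**What the plan says.** All references are to the protocol article.

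- **Eligibility (Criteria).** The study admits "patients who are treated by the endovascular approach for intracranial aneurysm(s"). No exclusion removes patients with several treated aneurysms.
- **Data recorded (Data collection and analysis).** The list of aneurysm characteristics ends with "whether the aneurysm is ruptured or unruptured, and the number of aneurysms".
- **Angiographic outcome (same section).** "Recurrence of aneurysms will be defined as any increase in contrast filling of aneurysms during follow-up".
- **Clinical outcome (same section).** This is assessed "using the modified Rankin scale score at 6 months", one value per patient. Age, smoking, hypertension and similar factors are also per patient.
- **Predictors (Geometric reconstruction; Computational fluid dynamics simulations).** Packing density is a ratio of coil volume to aneurysm volume. "Haemodynamic parameters will be carefully examined at two regions: the aneurysm neck plane and the aneurysm dome". Of the reduction ratio, the text says "This is a normalised parameter to allow comparison among different patients".
- **Sample size and data analysis.** The study is sized as 150, then 167, then 200 patients, on the basis that "the recurrence rate of aneurysms was approximately 10" per cent. Associations are tested by t-test, Wilcoxon, chi-squared or Fisher test, and then: "Logistic regression will include all variables with p<0.20 by univariate analysis".

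The article names no unit of analysis, no rule for a patient with two treated aneurysms, and no clustered method.

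**The concern.** Consider a patient with two treated aneurysms, one recurrent and one stable. The eligibility criteria admit this patient, but the named analysis can take the data in only two ways:

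- **One row per aneurysm.** The rows are not independent. They share patient risk factors and may share the Doppler inflow waveform, which is measured per patient. Patient-level factors are copied exactly onto both rows.
- **One row per patient.** Someone must decide which aneurysm supplies the recurrence status, packing density and velocity reduction. No rule is given, so the choice could be made after the results are known.

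The first route makes confidence intervals too narrow and p-values too small, and it loosens the p<0.20 screen that decides which variables enter the model. The second leaves room for selection. At a 10% recurrence rate only about 15 recurrences are expected in 150 patients (20 in 200), so a few records could change which variables pass the screen.

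**Working it through.** **1. Reproduce the plan's sample size.** Inputs from Sample size and data analysis: mean reduction 20% (SD 10) with recurrence and 30% (SD 15) with stability, recurrence 10% (ratio 1:9), two-sided 5%, power 80%.

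- Average variance: (10² + 15²)/2 = 162.5, so SD = 12.75.
- Recurrent group: (1.960 + 0.842)² × 162.5 × (1 + 1/9)/10² = 14.2, rounded up to 15.
- Stable group: 9 × 15 = 135. Total 150, which matches.
- Allowance for 10% loss: 150/0.9 = 166.7, rounded up to 167, which matches.

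The calculation therefore treats 150 patients as 150 independent records, with a group split taken from a rate of aneurysms.

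**2. Inputs that the documents do not give.** Assumed: a share s of 10–30% of patients has two treated aneurysms and the rest have one. The within-patient correlation is 0.3–0.5 for the outcome (ρy), and also for a predictor measured on the aneurysm (ρx). For a patient-level factor ρx = 1.

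**3. Formulas.** For a test of association, the variance inflation depends on the product of the two correlations:

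- Excess cluster size: k = (1 + 3s)/(1 + s) − 1 = 2s/(1 + s). This is 0.182, 0.333 and 0.462 for s = 10%, 20% and 30%.
- Design effect: DE = 1 + k × ρx × ρy.
- True two-sided error: 2 × [1 − Φ(1.96/√DE)].

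**4. Results if every aneurysm is analysed as an independent row.**

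| Predictor | ρx × ρy | s = 10% | s = 20% | s = 30% |
|---|---|---|---|---|
| Aneurysm-level, 0.3 and 0.3 | 0.09 | DE 1.02, 5.2% | DE 1.03, 5.3% | DE 1.04, 5.5% |
| Aneurysm-level, 0.5 and 0.5 | 0.25 | DE 1.05, 5.5% | DE 1.08, 6.0% | DE 1.12, 6.3% |
| Patient-level, outcome 0.3 | 0.30 | DE 1.05, 5.6% | DE 1.10, 6.2% | DE 1.14, 6.6% |
| Patient-level, outcome 0.5 | 0.50 | DE 1.09, 6.1% | DE 1.17, 7.0% | DE 1.23, 7.7% |

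With one record per patient, DE = 1 and the error stays at 5%.

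**5. Simulation check.** A pooled t-test was simulated with 150 patients, 10% recurrence and an aneurysm-level predictor. With s = 10–30% and correlations of 0.3–0.5, its error was 4.9–5.9%. The outcome correlation was set on an underlying continuous scale and is weaker once the outcome is made binary, so slightly lower values than in the table are expected.

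**6. Power.** Effective observations from 150 patients are 150 × (1 + s)/DE. Over the patient-level rows of the table, which have the larger design effects, this runs from 151 (s = 10%, product 0.50: 165/1.091) to 171 (s = 30%, product 0.30: 195/1.138). Second aneurysms add information, so the information available does not fall below that of 150 independent records.

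**The case against.** The strongest case against has three parts.

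**Silence is not an error.** Handling of several lesions per patient is often settled in a full protocol or an analysis plan, and only a condensed article is at hand. The sample size and the remark on comparing patients suggest one record per patient, under which every named test is valid. This stands as a limit on the claim: the documents not shown may resolve it. It does not remove the point, because the article itself counts patients in one place, defines outcome and predictors on aneurysms in another, and then fixes tests that cannot take a patient whom it admits without a further rule.

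**A reader might infer that the standard errors will be wrong.** The text does not support that. The error arises only if several aneurysms per patient enter as separate rows, which the article neither states nor excludes. Nor is everything measured per aneurysm: the modified Rankin score and the risk factors are per patient.

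**The multiplicity may be small and the effect modest.** Recording the number of aneurysms does not show that several were treated, and patients with earlier endovascular aneurysm treatment are excluded. This also stands. A reader might compute an error of about 9% for a patient-level factor, from 20% of patients with two aneurysms and DE = 1 + 0.333 = 1.33. That figure requires the outcome to be fully shared as well, as when a Rankin score is copied onto two rows. Nothing in the article plans this, and it does not fit recurrence, which can differ between two aneurysms in one patient.

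**Conclusion.** The point holds as an unresolved and inconsistent unit of analysis, not as a demonstrated error in the planned p-values. If all treated aneurysms were analysed as independent, the inflation of a 5% test would be modest: to about 5.2–6.3% for the haemodynamic predictors that are the study's main interest, and about 5.6–7.7% for patient-level factors. Both ranges rest wholly on the assumed 10–30% of patients with two treated aneurysms and correlations of 0.3–0.5, since the article supplies neither. The stated 150 and 167 reproduce and need no enlargement on this account. A change is still worthwhile because it is cheap, and because an open choice of aneurysm matters when few recurrences are expected.

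**What to change.** Add one or two sentences to Sample size and data analysis:

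- State that the aneurysm is the unit for angiographic outcomes. Analyse these with patient-clustered methods (logistic GEE or cluster-robust standard errors) in both the p<0.20 screen and the multivariable model.
- Alternatively, pre-specify one index aneurysm per patient, for example the largest treated. The named tests can then stay as they are.
- In either case, analyse the modified Rankin score with one record per patient.

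The clustered analysis can be run in the software already named. The cost is slightly wider intervals under the clustered option, or the loss of second aneurysms under the index option.

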### Geometric reconstruction and modelling techniques

All pre-embolised and post-embolised 3D aneurysm geometries will be obtained from digital subtraction angiography images.^7^
^8^
^14^ We will first segment and surface-smooth the images using Geomagic Studio, V.12.0 (Geomagic, Research Triangle Park, North Carolina, USA) and save the surface geometries in standard tessellation language format. As described in a previous study, the entire aneurysm model will be accurately and consistently separated into two regions: the aneurysm dome region that is embolised with coils, and the residual neck and parent vessel region.^14^

The porous media method will be used for intra-aneurysm coil modelling in the aneurysm dome region.^14^
^19^ Briefly, the aneurysm dome will be filled with porous medium corresponding to the coil mass, and the remaining vessel volume will be filled with fluid as blood flow. Packing density is defined as the ratio between the volume of the coils and the volume of the aneurysms. The parameter settings for coil modelling will be calculated based on the packing density.^14^
^19^
^20^

If a stent is used in clinical treatment, a novel virtual stenting workflow will be used to model intracranial stent deployment.^14^
^20^
^21^ Briefly, the workflow consists of three steps. (1) Pre-processing isolates the parent vessel and generates a simplex mesh structure along the vessel centre line. (2) Simplex mesh expansion occurs when the simplex mesh radially expands using mathematical forces. When the deployed simplex mesh has good apposition with the parent vessel wall, the deployment stops. (3) Post-processing maps and sweeps the stent into the final structures according to the types of devices. Finally, the post-embolised aneurysm model will be created using a porous media method and virtual stenting technique appropriately.

### Computational fluid dynamics simulations and haemodynamic analysis

The simulations will be performed as described in our previous studies.^14^
^20^ To create finite-volume elements for computational fluid dynamics (CFD) simulation, the deployed stent will be merged with the aneurysm geometry using mesh generation software (ICEM CFD, V.14.0; ANSYS Inc, Canonsburg, Pennsylvania, USA). The largest element will be 0.2 mm. The element size on the stent will be set to approximately one-third the width of the strut of the stent for adequate representation of stent geometry. Mesh sizes will be <3 million elements for untreated cases and 10 million elements for treated cases. The ANSYS CFX 14.0 (ANSYS Inc) will then be used to solve the flow-governing Navier-Stokes equations. Some assumptions, like laminar, incompressible, Newtonian blood flow, and vessel wall will be rigid with no-slip boundary conditions, and will also be applied. The density and dynamic viscosity of blood flow will be set at 1060 kg/m^3^ and 0.004 N·s/m^2^, respectively. The pressure distribution along the parent vessel and aneurysm will then be computed by using the fall in pressure that is calculated during the CFD simulations with respect to the p=10 000 Pa value prescribed at the outlets.^22^
^23^ The patient-specific pulsatile velocity waveform, which will be obtained by transcranial Doppler in every patient, will be applied for the inflow boundary condition. The flow waveforms will be scaled to achieve a mean inlet wall shear stress of 15 dyne/cm under pulsatile conditions.^23^ Three cardiac cycle simulations will be performed because of numerical stability and the last cardiac cycle will be collected as output.

We will then post-process and visualise the results of these simulations with the ANSYS CFD-Post. Haemodynamic parameters will be carefully examined at two regions: the aneurysm neck plane and the aneurysm dome. These parameters are wall shear stress, velocity, and pressure. The averaged and maximum values will be recorded. In addition to quantitative parameters, the qualitative parameter as inflow concentration will also be recorded. As described by Dhar *et al*,^24^ with estimation using multiple views of aneurysm geometries, the IA neck plane will be defined and created as the location from where the aneurysm sac pouches outward from the parent artery. Because flow in aneurysms before and after embolisation is different in each case, we will use the reduction ratio, which is calculated as: (parameter_pre_−parameter_post_)/parameter_pre_. This is a normalised parameter to allow comparison among different patients.^14^

